### Study population and eligibility criteria

Two hundred and seventy patients diagnosed with a solid malignancy, presenting the following histologically confirmed cancers: metastatic breast, lung, prostate, head and neck, endometrial, clear renal cell, pancreatic and urothelial cancer as well as locally advanced or metastatic ovarian cancer. Two hundred and thirteen are expected for STEP 2. Study inclusion and exclusion criteria are detailed in Tables 1 and 2.

**Table 1 Tab1:** General and cohort specific study inclusion criteria

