### Statistical analyses

Continuous variables will be summarized using descriptive statistics, i.e. number of subjects with available data (N), mean, median, standard deviation (S.D.), 25–75% quartiles (Q1-Q3) and range. Continuous variables could be transformed as categorical variable using median or using conventional cut-off from bibliography or clinical practice. If required comparison using Chi square (or exact Fisher test) or Student T test (or Wilcoxon Mann and Whitney) tests will be done. Categorical variables will be described by and percentages. The number of missing data will be described.

Each cohort will be described and analyzed separately.

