#### Sample size calculation

Sample size was determined using an A’Hern’s single stage design. The primary endpoint is progression PFS. It will be evaluated at 6 months (except for ovarian cancer with an evaluation at 18 months given the results of olaparib in SOLO-2 trial). The hypotheses are the following:
one-sided alpha risk =10%, a power = 90%,the expected rate of patients stable or in response after 6 weeks of olaparib is 80%,the expected rate of patients non-evaluable the primary endpoint is 5%,P0 and P1 are determined using hypotheses detailed above.

P0 is the highest level of inefficacy for which the new treatment will be rejected (maximal inefficacity). P1 defines the minimum required level of efficacy. The design of the trial focuses on demonstrating that this level is plausible given that the trial results and the efficacy is greater than the first proportion, P0. Taking into account these hypotheses: 270 patients will be included in the study, and at least 213 are required for statistical analyses. At the end the study, analysis of the primary endpoint will be performed on evaluable patients who were in response or stable after 8 weeks of olaparib.

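### With 80% passing STEP 1 and 5% non-evaluable, 270 enrolled patients give about 205 evaluable, not 213, and the article uses 213 for both STEP 2 entrants and patients analysed

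*Protocol article*

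**What the plan says.** In the Protocol article, Sample size calculation:

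- The design: "Sample size was determined using an A’Hern’s single stage design", with "one-sided alpha risk =10%, a power = 90"%.
- The first loss: "the expected rate of patients stable or in response after 6 weeks of olaparib is 80"%.
- The second loss: "the expected rate of patients non-evaluable the primary endpoint is 5"%.
- The result, presented as following from these hypotheses: "270 patients will be included in the study, and at least 213 are required for statistical analyses".
- The success rates: "P0 and P1 are determined using hypotheses detailed above". No value of P0 or P1 is printed there or elsewhere in the article.

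The same section restricts the primary analysis to evaluable patients who passed STEP 1, so both losses lie between enrolment and analysis.

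Study population and eligibility criteria gives the same number another meaning: "Two hundred and thirteen are expected for STEP 2". The abstract also attaches 213 to the patients in whom the triple combination is assessed.

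On the unit of analysis, Statistical analyses says: "Each cohort will be described and analyzed separately". Table 1 lists nine tumour-specific cohorts. Their sizes are not given.

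**The concern.** A total said to take account of two losses should return the required number when both are applied. This one does not. The figure called the minimum for analysis is close to what 270 gives after the first loss alone, and the Study population section does use it for that earlier stage.

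The required number of evaluable patients is what a single-stage exact design rests on. If it is 213, the trial is expected to finish below its own stated minimum. If it is lower, the article misstates the requirement, and a reader comparing the final count with 213 would wrongly conclude that the trial fell short.

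**Working it through.** **Inputs.** 270 enrolled, 213, 80% and 5%, one-sided alpha 10% and power 90% (all from Sample size calculation); 213 as STEP 2 entrants (Study population); nine cohorts (Table 1).

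**1. Forward from 270.**

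- STEP 2 entrants: 270 × 0.80 = 216.
- Evaluable: 216 × 0.95 = 205.2.
- Shortfall against 213: 213 − 205.2 = 7.8, or 3.7%.
- If the 5% is taken of all enrolled patients: 270 × 0.75 = 202.5, further below 213.

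**2. Backward from 213: can 270 be reproduced?**

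| Route | Result | Rounded up |
|---|---|---|
| Both losses, 213 / (0.80 × 0.95) | 280.3 | 281 |
| Both losses, 5% of enrolled, 213 / 0.75 | 284.0 | 284 |
| STEP 1 loss only, 213 / 0.80 | 266.25 | 267 |
| 20% added instead of divided out, 213 × 1.2 / 0.95 | 269.05 | 270 |

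No correct use of both losses after 213 gives 270. The third route comes within rounding by cohort. The fourth hits 270 exactly, but inflates for the 20% loss wrongly. The article does not show which was used.

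**3. What 213 analysed out of 270 would require.** 213 / 270 = 78.9% retained, against the planned 0.80 × 0.95 = 76%. With the 5% loss kept, the STEP 1 pass rate would have to be 0.789 / 0.95 = 83.0%. At 76% retention, the binomial probability of 213 or more evaluable from 270 is about 15%.

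**4. The two uses of 213.**

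- If 213 enter STEP 2: 213 × 0.95 = 202.4 are evaluable, so 213 is not the number analysed.
- If 213 are analysed: 213 / 0.95 = 224.2, so 225 must enter STEP 2, and 213 is not the number of entrants.

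**5. Power, only if 213 is the evaluable minimum.** Suppose that 213 gave exactly 90%. Normal scaling on the total gives, for 205.2:

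Φ[(1.2816 + 1.2816) × √(205.2/213) − 1.2816] = Φ(1.234) = 0.891, a loss of about 0.9 points.

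Power attaches to each cohort, however. The table takes **assumed** P0 and P1, finds the smallest exact design with alpha ≤ 10% and power ≥ 90%, reduces n by 3.7% (rounded), and sets the cut-off again at the smaller n.

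| P0 / P1 (assumed) | n | Power | Reduced n | Power |
|---|---|---|---|---|
| 0.10 / 0.30 | 25 | 0.9095 | 24 | 0.8889 |
| 0.20 / 0.40 | 36 | 0.9096 | 35 | 0.8877 |
| 0.20 / 0.45 | 24 | 0.9137 | 23 | 0.8848 |
| 0.30 / 0.50 | 39 | 0.9002 | 38 | 0.8721 |
| 0.30 / 0.55 | 25 | 0.9040 | 24 | 0.8659 |
| 0.40 / 0.60 | 41 | 0.9035 | 39 | 0.8287 |
| 0.40 / 0.65 | 29 | 0.9022 | 28 | 0.8572 |
| 0.50 / 0.70 | 39 | 0.9056 | 38 | 0.8631 |
| 0.50 / 0.75 | 26 | 0.9091 | 25 | 0.8506 |

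The reduced designs have power of about 83% to 89%, which is 1 to 7 points below the nominal 90%.

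**The case against.** The strongest defence is that 213 counts STEP 2 entrants and already contains the 5%. Suppose that about 202 evaluable patients are needed. Then 202 / 0.95 = 212.6, or 213 entrants; 213 / 0.80 = 266.25; and rounding up over nine cohorts could give 270. Both assumptions are used, and the expected 205 evaluable exceeds 202. The Study population section and the abstract favour this reading. On it, 270 × 0.80 = 216 entrants are expected, the chance of at least 213 is about 70% (normal approximation, mean 216, SD 6.6), and no power is lost. This stands as a possible account of the numbers. It does not clear the text, because the Sample size section would still be wrong to call 213 the minimum for analysis.

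A reader might go further and infer that the trial does not have its stated 90% power. The document does not support that. P0, P1, cohort sizes and cut-offs are not printed, power belongs to each cohort and not to the total, and under the benign reading there is no deficit. The power table shows only what could follow. Its falls are partly built in, since an exact design at its smallest n has little slack and its power moves unevenly with n. The average shortfall is also under one patient per cohort (7.8 / 9 = 0.87).

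Nor does the article say that a cut-off computed for the planned number would be kept at a smaller one. It states no cut-off, and setting one at the number reached may be in the full protocol or analysis plan.

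A journal article may leave P0, P1 and cohort sizes to the full protocol. Their absence is not the point here. The conflict lies between figures that the article does print.

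**Conclusion.** The arithmetic holds on the article's own figures. Under 80% and 5%, 270 enrolled patients are expected to give about 216 STEP 2 entrants and about 205 evaluable, 8 fewer than the 213 said to be required for analysis. On either reading, at least one stated sample-size figure is wrong:

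- **213 is STEP 2 entrants.** The analysed minimum should read about 202, and 270 is enough.
- **213 is the evaluable minimum.** The Study population statement is wrong, 270 is expected to fall about 8 short, and about 281 would be needed.

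The document does not settle which applies. A loss of power arises only under the second, and its size cannot be fixed from what is printed: about 1 point by normal scaling on the total, and roughly 1 to 7 points below 90% per cohort under the assumed P0 and P1 values. This is a correction to a figure that the trial relies on, not a demonstration that the trial is underpowered.

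**What to change.** Reconcile Sample size calculation with Study population and eligibility criteria. State what 213 counts and show the steps from the evaluable number required to 270.

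- If 213 is STEP 2 entrants: change the sentence on the number required for analysis to the evaluable number, about 202.
- If 213 is the evaluable minimum: correct the Study population sentence; state that 270 enrolled are expected to yield about 205 evaluable and that 213 would need about 281; and restate power for each cohort at the evaluable number expected, with the exact cut-off set for that number.

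The first case costs one sentence. The second costs a text correction and a re-run of the exact design in each cohort, with a somewhat lower stated power. Neither correction requires extra patients. Enrolment would rise towards 281 only if the sponsor confirms 213 as the evaluable minimum and chooses to keep it.

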### Study endpoints

The primary endpoint is progression free survival (PFS) 6 months after the initiation of immunotherapy for all cohorts, with the exception of ovarian cohort evaluated at 12 months. PFS is defined as the time from the date of first dose of immunotherapy to the date of progression or death from any cause. Progression will be defined using iRECIST criteria.

Secondary endpoints are:
Disease control rate, including stable and responsive disease, evaluated 6 months after immunotherapy initiation for all cohorts except ovarian cohort, evaluated at 12 months.Overall survival (OS) evaluated at 12 and 24 months after immunotherapy initiation defined by the time of the first immunotherapy dose to the date of death from any cause.Response rate evaluated by CT scan, RECIST evaluation after 6 weeks of olaparib therapy.Olaparib toxicity evaluated at the end of STEP1 using CTCAE V5.Olaparib + immunotherapy (tremelimumab + durvalumab) toxicity evaluated at 3, 6 and 12 months after immunotherapy initiation using CTCAE V5.

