**General step 2**		
12 CT Scan evaluation after 6 weeks of olaparib should present response or stable disease as defined by RECIST v1.1 criteria.		

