**Step 2**	
Patients should not enter the study if any of the exclusion criteria from STEP 1 and the following criteria for STEP 2 are fulfilled: 26 Patient with progression observed on CT scan performed after 6 weeks of olaparib (STEP 1).	

^a^ Except alopecia, ototoxicity, vitiligo, and laboratory values defined in inclusion criteria. Patients with Grade ≥ 2 neuropathy will be evaluated on a case-by-case basis after consultation with study physician. Patients with irreversible toxicity not reasonably expected to be exacerbated by treatment with olaparib or durvalumab or tremelimumab may be included only after consultation with study physician

^b^ Concurrent use of hormonal therapy for non–cancer-related conditions (e.g., hormone replacement therapy) is acceptable

^c^ Non-palliative radiotherapy within 21 days prior the first dose of study drug or within 6 weeks for therapeutic doses of MIBG or craniospinal irradiation. Palliative radiotherapy (which would be < 30% of the bone marrow) to non-target lesions is allowed

^d^ Patient with allogenic stem cell transplant within 3 months prior the first study dose of Olaparib are not eligible. Patient with myeloablative therapy with autologous hematopoietic stem cell rescue within 8 weeks of the first study drug dose are not eligible. Patients receiving any agent to treat or prevent graft-versus host disease ‘GVHD) post bone marrow transplant are not eligible for this trial

^e^ Except for: malignancy treated with curative intent and with no known active disease ≥5 years before the first dose of IP and of low potential risk for recurrence; adequately treated non-melanoma skin cancer or lentigo maligna without evidence of disease; adequately treated carcinoma in situ without evidence of disease and history of leptomeningeal carcinomatosis

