### Study procedures

All patients respecting all eligibility criteria, namely presenting mutations in homologous repair genes will be included. Regimens sequence is presented in Fig. 1. Study will be divided into two successive steps:
*Step 1*After 6-weeks of olaparib, all patients from STEP 1 will have a CT scan.*Step 2*Depending on CT scan results, two situations will occur:
Patients with stable disease or partial response will follow olaparib + immunotherapy by durvalumab + tremelimumab during 4 months and then continue with durvalumab alone until progression or until 24 dosing maximum of durvalumab for all cohorts except for ovarian cohort with a maximum of 36 dosing.Patient with progression will be withdrawn from the study and treated according to standard care.

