### Treatment doses and regimens

#### Olaparib

Patients will be administered olaparib study treatment tablets orally at a dose of 300 mg bid.

The maximum duration of treatment with olaparib is 8 weeks, corresponding to the duration of STEP 1, + 4 months, the duration of the initial part of STEP 2. The initial dose of 300 mg bid will be made up of 2 × 150 mg tablets bid. All doses of study treatment should be taken at the same time every day approximately 12 h apart.

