#### Durvalumab + tremelimumab combination therapy

Patients in the durvalumab + tremelimumab combination therapy treatment will receive durvalumab (1500 mg Q4W) in combination with tremelimumab (75 mg IV Q4W) for up to 4 doses/cycles each, followed by durvalumab 1500 mg Q4W until confirmed PD (progressive disease), unacceptable toxicity, consent withdrawal, or occurrence of events leading to treatment discontinuation. With a maximum of 24 dosing of durvalumab (36 dosing for ovarian cohort).

Tremelimumab will be administered first. Durvalumab infusion will start approximately 1 h (maximum 2 h) after the end of the tremelimumab infusion. Standard infusion time for each is 1 h.

The first durvalumab monotherapy dose at 1500 mg Q4W will be 4 weeks after the final dose of durvalumab in combination with tremelimumab. (Cycle 5). After 20 cycles, durvalumab will be stopped for all cohorts, except for the ovarian cohort for a maximum of 32 months with durvalumab.

All patients will be followed for disease progression and survival until 24 months after the end of treatment.

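### The primary analysis set is defined by status after 8 weeks of olaparib, but STEP 2 entry rests on a 6-week CT and the efficacy section defines a different set

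*Protocol article*

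**What the plan says.** All references are to the protocol article.

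- **Sample size calculation:** "analysis of the primary endpoint will be performed on evaluable patients who were in response or stable after 8 weeks of olaparib". The same section states the expected 80% rate of stable or responding patients at 6 weeks.
- **Study procedures, Step 1:** "After 6-weeks of olaparib, all patients from STEP 1 will have a CT scan".
- **Table 1, General step 2 (criterion 12):** "CT Scan evaluation after 6 weeks of olaparib should present response or stable disease as defined by RECIST v1.1 criteria".
- **Table 2, Step 2 (criterion 26), as an exclusion:** "Patient with progression observed on CT scan performed after 6 weeks of olaparib (STEP 1". The abstract also places the gate at 6 weeks.
- **Treatment doses and regimens, Olaparib:** "The maximum duration of treatment with olaparib is 8 weeks, corresponding to the duration of STEP 1", to which the sentence adds the 4 months of combination treatment in STEP 2.
- **Study endpoints:** "PFS is defined as the time from the date of first dose of immunotherapy".
- **Analysis of efficacy endpoint(s):** efficacy is analysed in a modified intent-to-treat population. Its members have had at least one dose of durvalumab plus tremelimumab and have a 6-month evaluation (12-month in the ovarian cohort). This definition has no condition on status at any week of olaparib.

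**The concern.** The rule in the sample size section needs a disease status at week 8 of olaparib, and the article describes no assessment that would supply it. It also does not match the rule that lets a patient into STEP 2, or the population named in the efficacy section. Two analysts following two sections could analyse different patients.

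The timing relative to the PFS origin matters more than the mismatch in wording. PFS starts at the first immunotherapy dose. If that dose is given on the strength of the 6-week CT, week 8 of olaparib is about 2 weeks into the regimen under test. Requiring a patient to be stable then conditions on the outcome: anyone who died or clearly progressed in those 2 weeks could be left out. That would push the landmark PFS rate up and make it easier to reject P0 when the regimen is no better than P0.

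The efficacy section has a similar weakness. Read literally, a patient who dies or progresses before month 6 and so has no 6-month evaluation is not in the set, although that patient is a failure.

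**Working it through.** **1. The stated sample size.** With 213 taken as STEP 2 entrants, 213 / 0.80 = 266.25, so 267, close to the planned 270. Forward, 270 × 0.80 = 216. The 80% is already stated at 6 weeks, so reconciling the 8-week wording changes no sample size figure. The A'Hern calculation behind 213 cannot be reproduced because P0 and P1 are not printed.

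**2. The two readings of week 8.**

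- STEP 1 lasts 8 weeks (Olaparib section) and immunotherapy starts at its end. Week 8 does not come after the PFS origin, the condition only restates who entered STEP 2, and no STEP 2 failure is removed. Bias: zero.
- Immunotherapy starts on the 6-week CT result (a possible reading of the abstract and Study procedures). Week 8 is about 14 days after the PFS origin, and failures in that window could be removed.

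**3. Upper bound under the second reading.** Assumptions, none of them from the article: constant hazard; true 6-month PFS (S6) of 0.30, 0.40 or 0.50, each taken as P0; P1 = P0 + 0.25; one exact single-stage design for each P0, with n patients and success declared at r or more without failure; n unchanged after removal; every failure in the 14 days removed.

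- Hazard per month: λ = −ln(S6) / 6
- Share failing in 14 days: F = 1 − exp(−λ × 14/30.44)
- Apparent rate after removal: S6 / (1 − F)
- Type I error: P(X ≥ r), with X binomial(n, rate)

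For S6 = 0.30: λ = 1.204/6 = 0.2007; F = 1 − exp(−0.2007 × 0.460) = 0.088; apparent rate = 0.30/0.912 = 0.329.

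| S6 = P0 | n, r | F | Apparent rate | Type I error, none removed | All removed | Half removed | One tenth removed |
|---|---|---|---|---|---|---|---|
| 0.30 | 25, 11 | 8.8% | 0.329 | 9.8% | 16.6% | 12.7% | 10.3% |
| 0.40 | 29, 16 | 6.8% | 0.429 | 7.1% | 12.6% | 9.5% | 7.5% |
| 0.50 | 26, 17 | 5.2% | 0.527 | 8.4% | 13.6% | 10.7% | 8.9% |

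The rate rises by 2.7 to 2.9 points. The power of these designs at P1 is 90–91%.

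**4. Sensitivity to the assumed design.** With P1 = P0 + 0.20 and P0 from 0.20 to 0.60, n is 36 to 41. Type I error then goes from 8.9–10.0% to 14.8–18.1% with full removal, and to 11.6–13.2% with half removed. The order of magnitude does not depend on the 25-point choice.

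**The case against.** The strongest reply is that the 8-week phrase is harmless. The Olaparib section gives STEP 1 a length of 8 weeks, so the phrase may simply mean the end of STEP 1 and describe the patients who went on to immunotherapy. On that reading there is no bias. This stands, and it is why bias cannot be claimed outright. It does not remove the contradiction: the gate is described at 6 weeks throughout, and the article does not say when immunotherapy starts relative to week 8.

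A second reply is that, with no week-8 scan, status can only be carried forward from the 6-week CT, so only deaths or clinical progressions could be dropped. Patients just shown by CT to be free of progression are also unlikely to fail at the average hazard from day 0. This stands too. The full-removal column is a ceiling, and with one tenth removed the type I error barely moves.

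A third reply is that the sentence sits under sample size and the efficacy section gives the real population. The article does not say which governs, and the efficacy section's set has its own condition on a later evaluation.

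Two stronger readings are not supported. A reader might infer that the primary analysis is shown to be biased; that follows only if STEP 2 starts before week 8. A reader might also infer, from the statement that the analysis takes place at the end of the study and from "All patients will be followed for disease progression and survival until 24 months after the end of treatment", that the result is wrongly delayed. The article promises no earlier analysis, plans no interim efficacy analysis and uses a single-stage design. A final analysis fits that, and its timing does not bias a landmark rate.

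**Conclusion.** The point holds as a conflict between the sections that fix the primary analysis set. One section uses status at 8 weeks of olaparib, which no described assessment supplies. The STEP 2 gate uses 6 weeks. The efficacy section drops the olaparib condition but requires a landmark evaluation. The set cannot be applied as written.

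The effect on the result is conditional: zero if immunotherapy starts at week 8. If it starts at week 6, the effect is at most about 3 points on the 6-month PFS rate, with one-sided type I error of about 13–17% in place of about 7–10%. Those figures rest on a constant hazard, on P0 and P1 chosen for illustration and on removal of every failure in 2 weeks; the realistic effect is smaller. The correction should be made because the rule is central and cheap to repair, not because a large bias has been shown.

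**What to change.** Use one primary set in both the Sample size calculation and the Analysis of efficacy endpoint(s) sections: all patients who received a first dose of immunotherapy, which is the PFS origin in Study endpoints. Attach no condition on disease status at a later week, and none on having a 6- or 12-month evaluation. State that deaths and progressions before the landmark count as failures. Changing only the sample size sentence would leave the evaluation requirement in the efficacy section in force.

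Separately, reconcile the 6- and 8-week statements in Table 1 (General step 2), Table 2 (Step 2), Study procedures, Olaparib and Sample size calculation, and say when immunotherapy starts relative to the CT. Which duration is right is for the trial team; this review takes no position.

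Cost: wording in two statistical sections and one reconciliation of the STEP 1 length. No extra patients or assessments are needed, and 270 and 213 are not altered by this change.
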